### Randomisation

Participants will be individually randomised, stratified by site, the presence of a co-resident carer and history of previous falls, using a dynamic, adaptive allocation algorithm [36] accessed by a secure web portal to the system held at the North Wales Organisation for Randomised Trials in Health Clinical Trials Unit (NWORTH CTU), Bangor University. The randomisation system will be maintained by a statistician independent of the analysis and research teams. Access to the study website will be password protected. After randomisation and irrespective of intervention group allocation, a member of the local research team will inform the participant about the treatment and follow-up plan and inform the therapy provider so a visit can be arranged.

### Blinding

Blinding of intervention is impossible for participants and therapists administering the intervention. Blinding of researchers to allocation during outcome assessment proved impossible in practice during the feasibility study, as participants frequently inadvertently unblinded the researcher (Goldberg et al., Promoting Activity, Independence and Stability in Early Dementia (PrAISED): a feasbility, multisite, randomised controlled trial, forthcoming). This problem has also been reported in similar trials [34]. Researchers collecting baseline and outcome data will therefore not be blinded to allocation. To minimise ascertainment bias, we will use specific awareness training to avoid bias of researchers and collection of hospital and resource use data. We will use a ‘case manager’ system for recruitment and data collection (having a single person undertake all assessments and act as the main point of contact for a given participant), which proposes to improve support to participants, aiming to maximise retention in the study.

Statistical analysis will be blind to allocation.

### Baseline data collection

Researchers will visit participants and their informants in pairs, simultaneously interviewing the participants and informant dyads individually to complete assessments. Assessments will include (see Table 1):
Demographic and social variablesMedical and falls history, including previous fractures, hospitalisation and drugs takenFrailty and falls (SHARE frailty assessment and falls diary) [50]Blood pressure, sitting and standing (Omron M6 comfort (HEM-7321-E) automatic sphygmomanometer)Cognition (MoCA, animal-naming verbal fluency task and Cambridge Neuropsychological Test Automated Battery) [48, 49]Mood (Hospital Anxiety and Depression Scale and Apathy Evaluation Scale) [42, 43]Activities of daily living (Nottingham Extended Activities of Daily Living questionnaire and Disability Assessment for Dementia [DAD]) [37, 38]Physical activity (Longitudinal Study of Ageing Amsterdam physical activity questionnaire and Misfit Shine accelerometer) [44]Quality of life (Dementia Quality of Life [DEMQOL], EuroQoL five-dimension three level [EQ-5D-3L] and EQ-5D-5L) [39–41]Balance and mobility (Berg balance scale, Timed Up and Go, dual-task Timed Up and Go) [45–47]Health and social care resource use (Client Service Receipt Inventory [CSRI]) [51]Carer strain (Caregiver Strain Index), carer health-related quality of life (EQ 5D-5L), participant service use (CSRI) [51, 52]Personality (Big Five Inventory-10) [53].

**Table 1 Tab1:** Health status outcomes measured at baseline and after 12 months

Outcome	Measured by	Respondent
Activities of daily living	DAD [37]	Informant
	NEADL [38]	Patient
Quality of life	EQ-5D-3L self [39]	Patient
	EQ-5D-5L proxy [39]	Informant
	DemQOL [40, 41]	Patient
	DemQOL proxy [40, 41]	Informant
Depression, anxiety and apathy	HADS [42]	Patient
	AES [43]	Informant
Physical activity	LAPAQ [44]	Informant
	Pedometer/accelerometer	Patient
Balance and mobility	Berg balance scale [45, 46]	Patient
	TUG [47]	Patient
	Dual-task TUG [47]	Patient
Cognition	CANTAB [48]	Patient
	MoCA [49]	Patient
	Verbal fluency (animal-naming task)	Patient
Falls, fractures and frailty	Diary	Patient and informant
	SHARE frailty assessment [50]	Patient and informant
Admissions to and days spent in hospitals and care homes	Diary	Patient
	Hospital records	
NHS and social service costs	CSRI [51]	Informant
Carer strain	CSI [52]	Informant
Carer health-related quality of life	EQ-5D-5L self [39]	Informant

*DAD* Disability Assessment for Dementia, *NEADL* Nottingham Extended ADL scale, *EQ-5D-3L* EuroQoL five-dimension, three-level (self), *EQ-5D-5L* EuroQoL five-dimension, five-level (proxy), *DEMQOL* and *DEMQOL proxy* Dementia Quality of Life, *HADS* Hospital Anxiety and Depression Scale, *AES* Apathy Evaluation scale, *LAPAQ* Longitudinal Ageing Study Amsterdam Physical Activity Questionnaire, *Pedometer* Misfit Shine 2, *TUG* Timed Up and Go, *CANTAB* Cambridge Neuropsychological Test Automated Battery, *MoCA* Montreal Cognitive Assessment, *CSRI* Client Service Receipt Inventory, *CSI* Caregiver Strain Index, *NHS* National Health Service

### Intervention

The trial will compare the active and control interventions. The development and content of the programme has been published [32].

### Active intervention

The intervention programme will be tailored to individual abilities, co-morbidities, interests and goals. The intervention includes progressive strength and balance exercises; functional activities and risk analysis, training and advice; and environmental assessment and dual-task training, delivered using a motivational approach [32]. We will use a specially developed stratification tool to determine the frequency of intervention sessions for each participant to enable them to sustain the programme. Participants will receive between 9 and 50 visits from the trained study therapists and rehabilitation support workers over 52 weeks to directly supervise exercise, assess progress and provide progressively challenging activities and exercises. The programme is tapered to encourage habit formation and the continuation of self-directed exercise and activity between supervised sessions and after the programme has been completed. An option to pause or suspend the programme will be allowed to account for individual circumstances (such as holidays, illness or bereavement).

Participants will be encouraged to perform their intervention programme for at least 3 h per week. Previous guidance suggests at least 150 min of physical activity to promote healthy ageing [54] and at least 180 min of balance-challenging and progressive strengthening exercise per week to prevent falls [55]. A similar intensity has also been shown to improve neuropsychological function [25]. Spouses, partners, family members or carers are encouraged to support or participate as each individual circumstance allows. To encourage persistence after the intervention sessions and regular supervision ceases, participants will be introduced to local exercise, activity and community classes.

### Control

The control intervention has been modelled on usual care, consisting of a fall prevention assessment and follow-up. Control participants will receive an initial therapy visit and assessment within 2 weeks of the research assessment (baseline). This visit will be 90 min in duration. A further two visits are permitted (each of 90 min) by either the assessing therapist or rehabilitation support worker in order to review actions or expand on any advice provided following the falls assessment (for example, to seek a medicine review with the participant’s general practice physician). The advice and recommended actions are prompted by the falls assessment [56] and include actions for the participant (e.g. wearing more suitable footwear), the therapists (e.g. referral to local services) or both. Each visit received by the control participant will be 90 min in duration and will be completed within 3 months. The control participants are seen by the same group of therapists who administer the intervention.

### Concurrent treatment

All other interventions will be permitted, in both study arms, including cognitive stimulation therapy, use of acetylcholine inhibitor or memantine drugs or referral to mental health, medical, rehabilitation or falls prevention services. There are no arrangements for ancillary or post-trial care beyond routine clinical care. There are no special arrangements for compensation for non-negligent harm resulting from trial participation.

### Follow-up and outcomes

Each participant will take part for 15 months. After 6 months, informants will be asked to complete the EQ-5D-5L proxy [39], DEMQOL-U items from the DEMQOL measure [41] and the Short CSRI [51] about the participant, via post, with telephone calls to prompt or support as needed. The main follow-up is after 12 months (+/− 4 weeks), when two researchers will visit the dyads at home to collect outcome data by interviewing the participant and informant separately (Table 1). In the feasibility study, the follow-up rate at 12 months was 80% without differential loss between arms (Goldberg et al., Promoting Activity, Independence and Stability in Early Dementia (PrAISED): a feasbility, multisite, randomised controlled trial, forthcoming).

Participants will keep a monthly diary for falls and service use between months 0 and 15, with telephone calls to prompt or support as needed. Therapists delivering the intervention sessions will not be permitted to use or prompt the use of the monthly diary for either study arm.

For falls, the incidence rate ratio will be compared for the intervention and control groups. For all other outcome measures, the standardised effect size estimate (*d*) of the difference between the groups’ follow-up scores will be based on analysis of covariance (ANCOVA), which will take into account the baseline scores on the measures. Data will be aggregated using mean score unless descriptive statistics show the data to be substantially skewed or non-normal.

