## Objectives and methods

The study objectives are to:
Determine whether the intervention reduces disability in ADLs; increases level of physical activity; improves balance, quality of life, mood and cognition; and decreases apathy, rate of falling, rate of hospital and care home admission, days spent in hospital and carer strainDetermine if the intervention is cost-effective, within the trial period, over the anticipated remaining lifespan of participants, using a social return on investment modelEvaluate the individual- and contextual-level mechanisms that contribute to study outcomes and evaluate the implementation of the therapy programme.

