### Adverse events

Adverse event (AE) monitoring will begin when a participant has been randomised and will continue for 15 months. We will record AEs which are defined as serious (involving death, life-threatening events, hospitalisation, significant disability or incapacity) or which are potentially related to the intervention or to exercise undertaken independently. Inter-current illness, progression of dementia, loss of function, hospitalisation and death are likely to be common in this population given their age and frailty. We will assess all reported AEs for severity and relatedness to the intervention.

The intervention group will have more contact with professional staff than the control group, and therefore greater opportunity to report AEs, presenting a potential bias. We will screen falls diaries and medical records to ascertain core AEs across both arms. For purposes of comparing the safety of the intervention, we will consider ’deaths’, ’hospital admissions’ and ’falls’ to be core AEs. These will be ascertained and analysed as part of the core research dataset, independently of incidental reporting, and should therefore be more robust to information bias.

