### Assessment of efficacy

Analyses will be conducted on an intention-to-treat basis. Missing data for outcome measures will be imputed, using multiple imputation, if more than 5% of the data are missing and data are shown to be missing at random.

We will compare the DAD scores between the intervention and the control groups, adjusting for stratifying variables and any baseline imbalances in an ANCOVA model. Adjusted mean differences between groups and standardised effect size estimates (equivalent to Cohen’s *d* [59]) will be calculated.

Rate of falls will be compared between the intervention and the control groups using the incidence rate ratio, from a negative binomial regression model, adjusted for baseline imbalance or variables with prognostic importance [60, 61].

Other secondary outcomes will be compared between the intervention and the control groups using ANCOVA to adjust for baseline imbalance or variables with prognostic importance.

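### Hospital and care home admissions and days in hospital fall under a blanket ANCOVA-with-d rule, although the objective for admissions is a rate

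*Protocol article*

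**What the plan says.** All places are in the protocol article.

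- **Objectives and methods** lists among the things the intervention should decrease: "rate of hospital and care home admission, days spent in hospital".
- **Baseline data collection, Table 1** has an outcome row "Admissions to and days spent in hospitals and care homes", with diary and hospital records as sources.
- **Follow-up and outcomes** assigns falls an incidence rate ratio. It then sets one rule for everything else, beginning "For all other outcome measures, the standardised effect size estimate", which is d. On the model, the same sentence says that "follow-up scores will be based on analysis of covariance (ANCOVA), which will take into account the baseline scores on the measures". The next sentence says data are summarised by the mean unless clearly skewed or non-normal.
- **Assessment of efficacy** compares falls "using the incidence rate ratio, from a negative binomial regression model". It then says: "Other secondary outcomes will be compared between the intervention and the control groups using ANCOVA", and makes no exception for counts. Missing outcome data are to be multiply imputed if more than 5% are missing and they are shown to be missing at random.
- **Adverse events** opens its safety comparison with "For purposes of comparing the safety of the intervention, we will consider" and names deaths, hospital admissions and falls as core events. It adds: "These will be ascertained and analysed as part of the core research dataset". No model is named there.

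**The concern.** Admissions and days in hospital are not scores taken at a visit. They accumulate over time, most people are likely to have few or none, and a few people have many. The protocol recognises this for falls, which come from the same monthly diaries, but not for admissions.

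Two things are at stake. First, the objective is a rate of admission, and a standardised mean difference in counts cannot be read as one. Its size depends on how common and how dispersed admissions are, as well as on what the intervention does. Second, ANCOVA on a count has no term for time at risk. Someone who dies or leaves early has had less time in which to be admitted, and the model does not know it. If that happened more in one arm, that arm would appear to have fewer admissions.

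**Working it through.** **1. Which rule applies.** The general sentence in Follow-up and outcomes has all outcome measures other than falls as its subject. Table 1 lists admissions and days among the outcomes. The efficacy section has one count model, for falls, and ANCOVA for the rest. No other model, rate ratio or exposure term is given for admissions or days.

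**2. Whether observed time will vary between people.** Planned participation is 15 months for everyone. The sample size section allows 23% attrition, the feasibility study had 80% follow-up at 12 months, and the adverse events section expects death to be common. Observed time will therefore vary between people. Nothing in the document says it will vary between arms.

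**3. How many people have no admissions (assumed inputs).** The document gives no admission rate, so I assume 0.3 to 1.0 per person-year, negative binomial dispersion k = 1.5, and a full 15 months (1.25 years):

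P(zero) = (1 + k × rate × 1.25)^(-1/k)

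- 0.3 per year: (1 + 0.5625)^(-0.667) = 0.74
- 0.5 per year: (1 + 0.9375)^(-0.667) = 0.64
- 1.0 per year: (1 + 1.875)^(-0.667) = 0.49

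A person with no hospital admission has no hospital days. At the two lower rates the median is therefore 0, and replacing the mean with the median would say little.

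**4. What d reports when there is a real effect.** Simulation: 184 per arm, gamma-Poisson counts, true rate ratio 0.7, 23% attrition in both arms at uniform random times, 600 runs per row. ANCOVA on the count is compared with negative binomial regression with a log observed-time offset (NB).

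| Rate per year | Dispersion | Mean d (ANCOVA) | Median rate ratio (NB) | Rejection, ANCOVA v NB |
|---|---|---|---|---|
| 0.3 | 1.5 | -0.16 | 0.70 | 33% v 33% |
| 0.5 | 1.5 | -0.20 | 0.70 | 46% v 42% |
| 1.0 | 1.5 | -0.25 | 0.71 | 69% v 59% |
| 0.5 | 0.5 | -0.22 | 0.70 | 54% v 54% |
| 0.5 | 3 | -0.19 | 0.69 | 43% v 32% |

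The rate ratio is recovered throughout. The d moves although the true effect is fixed.

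**5. Whether the comparison is biased when there is no effect.**

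- *Equal attrition, 23% in both arms:* ANCOVA rejects 5.0% to 5.2% and NB 4.2% to 5.3%. There is no inflation.
- *Assumed early exit of 12% v 22%, uniform in time:* mean observed fraction = 1 - 0.12/2 = 0.94 v 1 - 0.22/2 = 0.89. The ratio is 0.89/0.94 = 0.947, so raw counts show about a 5% reduction under equal rates. A separate simulation (400 trials, 175 per arm, 0.5 admissions per person-year) gave a difference of -0.026 admissions, and -0.026/0.5 = -5.2%. NB with the offset gave a median rate ratio of 0.987.
- *Assumed attrition of 13% v 33%:* ANCOVA rejects 8.8%, 9.2% and 11.0% at 0.3, 0.5 and 1.0 admissions per year, and NB 4% to 5%. With 600 runs, the Monte Carlo standard error of a 5% rate is √(0.05 × 0.95/600) = 0.9 percentage points.

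**The case against.** **The sentence was written for scales.** It speaks of follow-up scores and baseline scores, which suggests its authors had questionnaires in mind. That may be so. But its subject is every outcome other than falls, and the efficacy section repeats the rule without mentioning scores. As written, the rule includes admissions and days.

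**Imputation would deal with early exit.** At 23% attrition the 5% trigger would be met, so it cannot be assumed that truncated counts would be analysed as if complete. This stands against any flat claim that early leavers simply count as having few admissions. But the rule does not say how a partly observed count is completed or what happens to time after death, and it names no count model. The skewness sentence names none either.

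**Leaving the visits need not end ascertainment.** Those who withdraw are asked to stay for outcome collection, and hospital records are a source in both arms. This narrows the variation in observed time. It does not remove the part due to death.

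**The only evidence on differential loss is against it.** The feasibility study reported none. A reader might infer that the comparison is biased towards the arm with more deaths or dropout. The document does not support that as an expectation. Even at 12% v 22%, the error is -0.026 admissions. With mean 0.5 and dispersion 1.5, the SD is √(0.5 + 1.5 × 0.25) = 0.94, so d is about -0.03.

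**Safety.** A reader might also infer that the safety comparison of hospital admissions is tied to ANCOVA. The adverse events section names no model. Of its three core events, falls already have a rate model, and deaths could have neither a baseline score nor a sensible d.

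**The offset is no cure-all.** It removes bias only if exit is unrelated to the risk of admission. In a frail population, where death may follow a hospital stay, that is not assured.

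**Conclusion.** The point holds for the wording of the analysis rule. The article states ANCOVA twice for everything but falls, and so for admissions and days, while its own objective for admissions is a rate. The mismatch is certain and needs no assumption about attrition. In the simulations, a fixed rate ratio of 0.7 appeared as a d between -0.16 and -0.25.

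Bias in the arm comparison is conditional. It needs observed time to differ by arm and truncated counts to enter the model unadjusted. The 5% figure and the rejection rates of 9% to 11% rest on assumed admission rates, dispersion and exit patterns, none of which the document gives. With equal exit, ANCOVA held its type I error near 5%.

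These are secondary outcomes, but they are named objectives, and hospital admissions are also a core safety event. That justifies correcting the rule before analysis. It does not support a claim that the primary result, or the safety comparison as planned, is wrong.

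**What to change.** In Follow-up and outcomes and in Assessment of efficacy:

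- limit ANCOVA with a standardised d to scale scores;
- analyse hospital and care home admissions as falls are analysed, by negative binomial regression, with a log observed-time offset, reported as a rate ratio with its confidence interval;
- analyse days in hospital with a model for skewed counts that includes observed time;
- state that observed time ends at death.

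If hospital admissions are compared between arms for safety, use the same rate model there and say so in the adverse events section. Finer choices, such as the exact model for days, can be left to the SAP.

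The cost is new wording and a little more analysis. Observed time per participant must be derived from the diaries and hospital records. The article does not say that event dates are recorded, so this should be checked. No power is gained: in the simulations the rate model rejected about as often as ANCOVA or less often (59% v 69% at 1.0 admission per year, dispersion 1.5). The gain is an estimate that matches the objective and allows for observed time.

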### Falls, programme adherence and service use

Adherence to the PrAISED programme, occurrence of falls and health and social care service use will be collected by monthly self-completed diaries. The nominated carer will be asked to prompt and oversee this task. Telephone calls will be made to prompt or support as needed.

### Process evaluation and motivation study

The process evaluation of the trial will follow Medical Research Council guidelines for the process evaluation of complex interventions [57]. It will be used to gather data around the implementation of the intervention, the mechanisms of impact and contextual factors and participants’ motivations [35].

The process evaluation will answer the question ’How does the intervention work?’ by identifying the mediating factors that contribute to study outcomes. It will use a mixed methods design and will comprise two studies. The implementation study will examine the training provided to therapists and how the intervention is delivered to participants, by looking at four domains:
Fidelity (the consistency of training and delivery of the intervention)Adaptations (alterations made to training and delivery, to achieve better contextual fit)Dose (how much training and intervention is delivered)Reach (the extent to which therapists and participants come into contact with the intervention).

The study on the mechanisms of impact and context will focus on the individual- and context-level mechanisms that contribute to study outcomes. These will be investigated through semi-structured interviews with participants and carers from each site. To ensure that the full range of perspective is gathered, we will purposively recruit participants with dementia/MCI from four different groups:
Low adherers to the PrAISED programme (i.e. participants who have undertaken less than 150 min of physical activity per week on average before the first set of interviews at month 6, as recorded on the calendar)High adherers to the PrAISED programme (i.e. participants who have undertaken more than 150 min of physical activity per week on average before the first set of interviews at month 6, as recorded on the calendar)Those who self-withdrawParticipants from the control group.

Clinicians will also be interviewed about their experiences of receiving training and delivering the intervention. Details of the process evaluation can be found in the published protocol [35].

Data from the qualitative interviews of the process evaluation will be used to investigate motivational factors linked to adherence.

